### Attrition and compliance

Due to the voluntary nature of the enrollment and that the subjects are older adults, the attrition rates of this study may be low. Considering other factors such as environment, health reasons, or other emergency situations, we expect a general attrition rate of 20 % in this study. Our recruitment plan takes this into account. To maximize compliance, retention in the study and adherence to treatment will be monitored prospectively and routinely throughout the trial.

### Study measurements

A structured interview and surveys will be used for the three groups at pre-intervention, post- intervention, and the follow-up to obtain self-reported outcomes. Although the participants will be aware of their study-group assignments, we will use the same format for interviews and surveys in the three groups to minimize ascertainment bias. Medical records will be obtained for their documentation of events. Whenever researchers become aware of an injury or accident, a standard protocol will be used to obtain information on the event. Demographic data will be collected at baseline. Clinical and laboratory measurements are performed at 2 weeks before starting the 6-month intervention (baseline), 1 week after completing the 6-month intervention, and at the 3-month follow-up. We also plan to compare the effects and outcome changes induced by Yi Jin Jing versus Tai Chi training on BPH.

### Study outcomes

Demographic information of the subjects will be collected, including age, body weight, body composition, resting heart rate, and resting blood pressure. The physical fitness of each subject will be tested and evaluated prior to and post the intervention. The primary outcome will be the exercise-induced changes of:Prostate volume, which will be measured using a Madison SA600P portable B ultrasound deviceBPH and LUTS symptoms, which will be measured using the international prostate symptom score (IPSS)Urination-related quality of life (Qol) before and after the intervention and at the follow-up

IPSS is identical to the American Urology Association (AUA) symptom index, which was developed by AUA in 1991. IPSS and Qol have been translated into many languages and are widely used around the world. The secondary outcomes are the blood chemical analyses of exercise-induced changes, which will be obtained at baseline, post-intervention, and at the 3-month follow-up. They are the circulating levels of fasting blood samples (2 mL, 12-hour fasting) and serum levels of sex hormones including dihydrotestosterone, progesterone, estrogen, testosterone propionate, and androgen, which will be measured using chemiluminescent magnetic enzyme-linked immunoassay systems. All the assessments will be performed in the laboratories of the Exercise Science College at the Shanghai University of Sport.

### Data management and statistical analysis

The baseline and later data will be collected and recorded after careful checking. Both quantitative and qualitative data, including the volume of the prostate, IPSS, Qol, and the level of sex hormones (dihydrotestosterone, progesterone, estrogen, testosterone propionate, and androgen), will be numerically coded and analyzed on an intention-to-treat basis. Participants who withdraw will be treated as having no change from baseline at all times after dropping out. Group differences at baseline will be tested using a two-sample *t*-test for quantitative data and a chi-square test for qualitative data. Repeated-measures analysis of variance (ANOVA) and Mann-Whitney *U* test analysis for each of the outcome variables will be conducted to determine the treatment effects in terms of within-group, between groups, and interactive group-by-time modes. Prior to further statistical analysis, parametric assumptions of normality and homoscedasticity for each variable will be checked using standard tests and graphical methods. According to the serum sex hormone test results, we will use MATLAB software to analyze the changes of serum E2/T ratio. This will probably allow us to develop further the fitted equation of the linear regression and create the three-dimensional graphics between the androgen levels and BPH for the changes in the measured scores before and during the Yi Jin Jing and Tai Chi exercise training, immediately on completing the intervention, and the follow-up. All statistical analyses will be performed using the Statistical Package for the Social Sciences (SPSS, Inc., Chicago, Illinois, United States) for Windows version 18.0. Unless otherwise noted, all data will be reported as mean ± SD. A level of *p ≤ 0.05* will be used for statistical significance.

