## Methods/Design

### Study design

To examine the effectiveness of the Yi Jin Jing exercise intervention on older adults, compared with Tai Chi training, we designed this study as a single-center repeated-measures randomized controlled clinical trial. Old subjects will be recruited from the community of Shanghai, China. With a 1:1:1 allocation ratio, enrolled eligible volunteers will be randomly assigned to three parallel arms including two intervention groups and a non-intervention control group (*n* = 50 per group). Participants in the two intervention groups will train with Yi Jin Jing or Tai Chi exercise continually for 6 months, while the control group will not receive any intervention. Assessments of the primary and secondary outcomes and data analysis will be performed at baseline, immediately after the 6-month intervention, and at the 3-month post-intervention follow-up. All tests and measurements will be conducted by trained professionals who are blinded to the group assignment of subjects and their specific background. The flow of participants through the trial is shown in Fig. 1.

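### Mann-Whitney U is assigned within-group and group-by-time effects that it cannot test, in a three-arm trial, with no rule on whether it or the ANOVA decides

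*Protocol article*

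**What the plan says.** Under Study design, the protocol article has participants "randomly assigned to three parallel arms including two intervention groups and a non-intervention control group". Assessments "will be performed at baseline, immediately after the 6-month intervention, and at the 3-month post-intervention follow-up". The data are therefore three arms by three times, with repeated values on each man.

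The section Data management and statistical analysis then names these methods:

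- **Baseline.** "Group differences at baseline will be tested using a two-sample" t-test "for quantitative data and a chi-square test for qualitative data".
- **Outcomes.** The sentence opens "Repeated-measures analysis of variance (ANOVA) and Mann-Whitney" and continues, after the U, with "test analysis for each of the outcome variables will be conducted to determine the treatment effects". The effects it has in view are given in the words "to determine the treatment effects in terms of within-group, between groups, and interactive group-by-time modes".
- **Assumptions.** Normality and equal variance are to be checked before further analysis. The article does not say what follows if a check fails.
- **Significance.** The level is p ≤ 0.05, with no adjustment mentioned for several comparisons.

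No paired rank test and no three-group rank test is named. Study measurements adds one comparison of particular interest: "We also plan to compare the effects and outcome changes induced by Yi Jin Jing versus Tai Chi training on BPH".

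**The concern.** Two methods are joined by a plain conjunction and given three aims, for every outcome. One of them, repeated-measures ANOVA, can serve all three. The other, Mann-Whitney U, can serve only part of one: an unpaired comparison between two arms.

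If the sentence is followed literally, each outcome gets two analyses and no rule says which is decisive. If Mann-Whitney is meant as the fallback when the ANOVA assumptions fail, the analyst is left with a two-group unpaired test for a design with three arms and repeated measures. This matters most for two of the three primary outcomes, the IPSS and urination-related quality of life. They are questionnaire scores, for which a rank method is a natural choice.

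**Working it through.** **Inputs from the protocol article.** Three arms, 1:1:1, and three assessment times (Study design); 40 evaluable men per arm and 20% dropout (Sample size); p ≤ 0.05 (Data management and statistical analysis).

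**Assumptions, because the article gives no figure.** Two-sided testing, normal data, pre/post correlation r from 0.5 to 0.9, and a change of 0.4 SD for the power illustration. Simulations used 20,000 runs.

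**1. The plan's own figure.** 40 / (1 − 0.20) = 50 per arm, and 3 × 50 = 150. This reproduces the stated total. The point about test choice does not change it.

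**2. Methods against aims.**

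| Aim | Repeated-measures ANOVA | Mann-Whitney U |
|---|---|---|
| Between three arms | Yes | Only two arms at a time |
| Within-group change | Yes | No, it treats paired values as independent |
| Group-by-time interaction | Yes, (3 − 1)(3 − 1) = 4 degrees of freedom | No such term |

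**3. Mann-Whitney on a man's own pre and post values.** The reason it goes wrong is easiest to see with means. Apart from the common factor 1/n, the variance of a pre/post difference is 2(1 − r)SD², whereas an independent-samples method uses 2SD². The ratio is 1/(1 − r):

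- r = 0.5: 1/0.5 = 2-fold too large
- r = 0.8: 1/0.2 = 5-fold too large

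An overstated variance makes the test conservative. As a rough guide, the effective critical value becomes 1.96/√(1 − r). At r = 0.5 this is 1.96/0.707 = 2.77, a two-sided rate of about 0.6%. Simulation of Mann-Whitney itself, one arm of 40, gave:

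| r | False-positive rate, Mann-Whitney | Power for 0.4 SD, Mann-Whitney | Power for 0.4 SD, paired t-test |
|---|---|---|---|
| 0.5 | 0.75% | 37% | 69% |
| 0.7 | 0.08% | 35% | 89% |
| 0.9 | about 0% | 31% | over 99% |

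The paired t-test held its level, at 5.1% for each r. The signed-rank test was not simulated, so the last column shows what pairing is worth and is not the exact power of the proposed replacement.

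**4. Mann-Whitney over the three arm pairs.** With no true difference and each pair tested at 0.05, the chance of at least one false positive would be 1 − 0.95³ = 14.3% if the tests were independent. The pairs share arms, so the true figure is lower. Simulation with 40 per arm gave 11.7% for Mann-Whitney and 11.9% for the t-test. A single three-arm one-way ANOVA gave 5.0%. These rates are for one variable at one time.

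**The case against.** The best reply has four parts.

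- **The sentence can be read more kindly.** It lists two methods and three aims without saying that each method serves each aim. The assumption checks in the next sentence suggest that Mann-Whitney is a fallback for between-arm comparisons. Which test applies to which pair is detail that an article may leave to a fuller document. This is a fair reading, and on it there are no two competing p-values. It does not remove the problem. The article never states the fallback, and the only rank method it names can give neither a paired result, nor an interaction, nor a single three-arm comparison. A fuller plan would have to replace that method, not merely add to it.
- **Two-sample tests are legitimate pair by pair.** This stands. Yi Jin Jing against Tai Chi is a stated interest, and Mann-Whitney on change scores would be valid for it. The article fixes neither the pairs, nor the use of change scores, nor the error control.
- **The baseline t-test has little consequence.** This stands too. Baseline differences between randomised arms arise by chance, and a false positive there changes no conclusion about efficacy.
- **The size rests on assumptions.** The correlation, the normal data and the 0.4 SD change do not come from the article, which also gives no distribution for the IPSS or quality-of-life scores.

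A reader might go further and infer that the named tests as a whole do not suit a three-arm repeated-measures trial, or that t-tests are to be used for within-group and interaction effects. The text does not support either. Repeated-measures ANOVA fits the design, the chi-square test handles three arms, and the t-test is confined to baseline. Nor does anything shown here count against the ANOVA or call for a mixed model in its place.

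**Conclusion.** The point holds for Mann-Whitney U and for the missing decision rule. The article names that test for purposes it cannot serve, on every outcome including all the primary ones. This is an error in what is written and not only a lack of detail.

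The size depends on use:

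- **Within an arm**, Mann-Whitney would be conservative. Its false-positive rate is below 1% at r of 0.5 or more, and it gives up much of the power of a paired analysis: 37% against 69% at r = 0.5, and 35% against 89% at r = 0.7, for a 0.4 SD change with 40 men. It could hide real change, but it would not create a false within-arm benefit.
- **Across all three arm pairs**, unadjusted use gives about 12% familywise error instead of 5%.
- **For interaction**, it gives no result at all.

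These figures assume normal data, two-sided tests and 40 evaluable men per arm. The defects in step 2 of the working need no such assumptions. The baseline t-test is a minor mismatch. Because a suitable method is already named beside the unsuitable one, this should be corrected but does not undermine the design.

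**What to change.** In Data management and statistical analysis:

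1. Keep repeated-measures ANOVA and state that its group-by-time term is the deciding analysis for each outcome.
2. Replace Mann-Whitney as the named rank method. For between-arm comparison, use Kruskal-Wallis on change from baseline across the three arms, followed by pairwise rank tests only if it is significant. For change within an arm, use the Wilcoxon signed-rank test. With three arms, the Kruskal-Wallis gate holds the familywise error near 5%: if all arms are equal the gate must first be passed, and if one differs at most one true null pair remains.
3. Label these rank tests either as sensitivity analyses or as the fallback if the assumption checks fail, and say which.
4. Remove the statement that Mann-Whitney addresses within-group or group-by-time effects.
5. Describe baseline by arm without significance tests.

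The cost is two or three sentences of text and slightly more analysis work. No further participants or measurements are needed.

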**Methods/Design:**

A prospective single-center randomized controlled trial will be conducted. A total of 150 old men (60–70 years old) will be recruited from the urban tertiary of Shanghai, China. Of these, 50 eligible participants will be randomly assigned to a control group and two intervention groups with either Yi Jin Jing or Tai Chi exercise training. They will undergo 30 minutes for each exercise for five times a week for 6 months. The primary outcomes are changes of signs and symptoms in BPH and lower urinary tract from baseline to post-intervention. The main secondary outcomes are exercise-induced effects on the circulating levels of estrogen and androgen. All the outcome measures will be assessed at baseline, immediately after the 6-month intervention, and at the 3-month post-intervention follow-up.

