### Sample size

The sample size was estimated using a randomized controlled trial about Tai Chi for LUTS and BPH [29] and we expanded the sample size to make it adequate to detect the expected changes of prostate volume. Ultrasound will be used to measure these changes before and immediately after the 6 months of Yi Jin Jing exercise training, and at the 3-month post-intervention follow-up. It is estimated that a sample size of 40 participants per group will be required to observe a similar result with a power of 80 %. Considering a 20 % dropout and exit rate, we will recruit 150 subjects with 50 in each group.

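### Within-group change and a between-groups ANOVA term are listed as treatment effects beside the group-by-time interaction, with no statement of which one decides

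*Protocol article*

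**What the plan says.** The section Data management and statistical analysis names repeated-measures ANOVA and the Mann-Whitney U "test analysis for each of the outcome variables will be conducted to determine the treatment effects". It then specifies "treatment effects in terms of within-group, between groups, and interactive group-by-time modes". The three modes stand side by side, with no order of priority.

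Study design describes a repeated-measures trial in three parallel arms, where "data analysis will be performed at baseline, immediately after the 6-month intervention, and at the 3-month post-intervention follow-up". That gives three visits: baseline, month 6 and month 9.

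On the target, the abstract states: "The primary outcomes are changes of signs and symptoms in BPH and lower urinary tract from baseline to post-intervention". Study outcomes is wider, because its list of primary outcomes also mentions the follow-up.

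The only stated use of baseline as such is a significance test: "Group differences at baseline will be tested using a two-sample" t-test or a chi-square test. No baseline covariate is named.

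**The concern.** The three listed modes answer different questions, and only one of them is sound here as a test of efficacy.

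- **Within-group change** compares an arm with its own past, so it discards the control arm that randomisation provides. Trial status puts baseline in February 2016 and the start of training in March, so the post-test falls about half a year later. Seasonal drift and regression to the mean both enter the change. Participants know their allocation (Randomization; Study measurements), and the symptom and quality-of-life outcomes are self-reported, so expectation enters too. Expectation matters less for ultrasound volume read by blinded staff.
- **The between-groups main effect** averages each man's visits. If baseline is one of them, a visit at which randomisation makes the expected difference zero is averaged in, and the variance between men remains.
- **The group-by-time interaction** compares change between arms, which is a proper randomised comparison.

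Because no mode is named as decisive, a null result on the diluted term could hide a real effect, and a significant within-arm change could be read as one.

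**Working it through.** **The plan's own figure.** Sample size requires 40 men per group for 80% power and allows for 20% dropout: 40 / (1 − 0.20) = 50 per group, 150 in total. This reproduces. The 40 itself cannot be rebuilt, because no difference, SD or correlation is given.

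**Inputs.** From the protocol: n = 40 per arm, 80% power, significance level 0.05, three visits. Assumed: a two-sided test, compound symmetry with between-visit correlation r = 0.5, 0.7 or 0.8, a two-arm comparison, and no true difference at baseline.

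**Calibration.** With n = 40 per arm, a two-sample t-test has 80% power at a standardised difference of 0.634. The SD of a change score is SD·√(2(1−r)). The difference giving 80% power on change scores is therefore δ = 0.634·√(2(1−r)) SD, which is 0.634, 0.491 and 0.401 SD at the three correlations.

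**Between-groups term, baseline included, effect sustained.**
- It estimates (0 + δ + δ)/3 = 2δ/3.
- The SD of a three-visit mean is SD·√((1+2r)/3) = 0.816, 0.894 and 0.931 SD.
- Standardised sizes are 0.518, 0.366 and 0.287.
- If the effect halves by follow-up, the term estimates (0 + δ + δ/2)/3 = δ/2.

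**Group-by-time interaction.**
- The noncentrality is λ = (n/2)·S / [SD²(1−r)], where S is the sum of squared deviations of the arm difference over the three visits.
- Sustained effect: S = 2δ²/3, so λ = 20 × (2/3) × 2 × 0.634² = 10.72.
- Halved effect: S = δ²/2, so λ = 20 × (1/2) × 2 × 0.634² = 8.04.
- With 2 and 156 degrees of freedom, power is 0.835 and 0.711. In this calibration r cancels.

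**Baseline-adjusted month-6 contrast.**
- The size is δ / [SD·√(1−r²)] = 0.732, 0.688 and 0.668.
- Its variance relative to a change score is (1−r²)/(2(1−r)) = (1+r)/2 = 0.75, 0.85 and 0.90.

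| Power, n = 40 per arm | r = 0.5 | r = 0.7 | r = 0.8 |
|---|---|---|---|
| Between-groups term, sustained effect | 63% | 37% | 25% |
| Interaction, sustained effect | 84% | 84% | 84% |
| Interaction, effect halves by follow-up | 71% | 71% | 71% |
| Month-6 contrast adjusted for baseline | 90% | 86% | 84% |

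**A second calibration** fixes the difference at 0.626 SD of the month-6 value, the size implied by 40 per arm under the normal approximation. At r = 0.5 and 0.7 with a sustained effect:
- between-groups term: 0.62 and 0.54;
- interaction: 0.83 and 0.97;
- adjusted contrast: 0.89 and 0.97.

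The ordering is the same.

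**Within-group change.** Suppose a shift of 0.3 SD common to all arms and no treatment effect. In one arm of 50, the standardised change is 0.3/√(2(1−r)) = 0.30 at r = 0.5 and 0.39 at r = 0.7. A paired test then gives p < 0.05 with probability 0.55 and 0.77. The 0.3 SD is an illustration, not a figure from the protocol.

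**The case against.** The strongest reply is that the right test is already planned. The interaction compares change between arms, and baseline works inside it by removing stable differences between men. Its power under these assumptions is close to that of the adjusted contrast: 6, 2 and 0 points lower when the effect is sustained. This stands. A reader might infer that the planned analysis as a whole dilutes the effect and wastes much power. The documents do not support that, because the dilution belongs to one of the three listed terms.

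A second reply is that the text never says that baseline is a level of the time factor. That is true. But with three visits, outcomes defined as change from baseline and a within-group mode, it is hard to read otherwise. The within-group point does not depend on this reading.

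Third, a test covering both later visits may be what is intended, since Study outcomes mentions the follow-up while the abstract stops at post-intervention. This also stands, and it is a reason to report both contrasts rather than fault the interaction for covering two visits.

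Fourth, an article commonly leaves covariates and the primary contrast to an analysis plan. That would excuse silence. Here the article names the method and lists what counts as a treatment effect.

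Finally, a reader might infer that efficacy will be claimed from within-arm change alone. Nothing says so: a no-intervention control arm and a Yi Jin Jing versus Tai Chi comparison are both planned. The fault is that the wording permits such a claim.

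**Conclusion.** The point holds in a limited form. The protocol counts as treatment effects one quantity with no comparator and one term that, if baseline is a time level, recovers two thirds of a sustained effect and half of one that halves by follow-up. It does not say that the interaction takes precedence over them.

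Relying on the between-groups term would cost much power: 63%, 37% and 25% against a design value of 80%. Relying on the interaction would cost little if the effect lasts. If the effect halves by follow-up, the interaction falls 19, 15 and 13 points below the adjusted contrast. Some loss is conceivable, since after month 6 participants are only asked to continue exercising.

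The sizes rest on assumed correlations, compound symmetry and an assumed follow-up profile. The direction does not change over the range examined: the adjusted contrast was never the weaker test.

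**What to change.** In Data management and statistical analysis:

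1. Define the treatment effect as the between-arm difference at month 6 adjusted for baseline, with a 95% CI. Use ANCOVA, or a mixed model with baseline as covariate, months 6 and 9 as outcomes, and the arm contrast read at month 6.
2. Report the same contrast at the 3-month follow-up, because Study outcomes includes that visit.
3. Report within-group changes descriptively, without calling them treatment effects.
4. Do not use a group main effect that averages in baseline as a test of efficacy.

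The cost is analysis wording only. Baseline is already measured on every man, and no visit, measurement or software need be added.
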